### Theoretical frame

As previously mentioned, spreading the ECAC advice and trying to change behaviors using the Internet to avoid behavioral cancer risk are already justified aims. However, this initiative could possibly fail if we do not bear in mind a psychological model that explains the possible risk behaviors. On the one hand, we should mention the A.S.E. Model (or I-Change Model), which was developed by de Vries group [27]. This model affirms that the purpose of carrying out a behavior mainly depends on three determining factors: attitude, social influence and self-efficacy (Figure 1). On the other hand, another well-known model among researchers is the Transtheoretical Model of Behavior Change, which was created by Prochaska and DiClemente [28]. This points out that the shifting from one risk behavior to a healthy one involves several stages of change. Both models have been used for the design of the educational tool.

**Figure 1 F1:**
[figure not shown]
Brief graphic explanation of the A.S.E. Model.

### Educational intervention

The main tool for the implementation of the intervention is a website designed by experts in the field of Health Education, and which has been adapted for Spain (http://www.alertagrumete.com) and Mexico (http://www.alertagrumete.com.mx).

In a previous stage, a qualitative research into a focal group formed by Spanish students was carried out in order to find out their likes and preferences. The result was a website with an animated interface and bright colors, and which is inspired on pirates. Users are identified with a captain who fights to avoid the boarding of the ship by a crab, which symbolizes cancer (Additional file 1 and Figure 2). The contents and aims of each section of the website are summarized below:

•*Challenge chest*. This is the most important area from an educational standpoint. Every week during the academic year, students are provided with a challenge or problem to be solved, which is adapted (a) to their curriculum, (b) to their educational level and (c) to cancer prevention. The challenges were devised by Secondary Education teachers who had previously attended a training course about Health Education. The main aim of the challenges is to impact positively on students’ attitudes and self-efficacy, as well as to encourage them to follow ECAC advice. An example of a simple challenge addressed to the youngest pupils is the following: ‘*Tobacco and potato plants can be cultivated on the same field*. *If four million hectares of tobacco were replaced by potato plants*, *how many millions of tons of the latter could be harvested to reduce hunger in the world*, *having in mind that in one square meter an average of 10 kg of potatoes could be collected*? *Correct answer*: *400 million tons*’.

•*Diet Analysis*. Diet experts perform different tasks. They: (a) analyze recipes, (b) collect 24-hour food recalls sent by the students, and (c) provide online dietary advice. Its main target is to achieve a positive attitude towards preventive diets, while highlighting their many advantages.

•*Library and links*. This is an information access point, in which relevant documents and links related to epidemiology and cancer prevention are included. Students must read these references in order to solve some of the weekly challenges and to be informed about the most important events related to the program. Part of the information provided focuses on the acquisition of knowledge, while another part focuses on attitudes and social influences.

•*Games*. The computer games that appear in the program are based on the ECAC advice and aim to encourage adolescents to memorize this advice as they play. All the games provide positive feedback and emphasize the importance of putting into practice the healthy behaviors that the game suggests.

•*Videos*. They are short videos of students, imitating TV commercials. They aim to promote positive attitudes and social influence regarding the following of ECAC advice.

•*Forum and chat*. It is an open discussion forum about cancer prevention, where students are asked to give their opinion about the advantages and disadvantages of following the ECAC advice. The forum tries to promote the attitudes and social influence of their participants. This section also includes a chat room, with access control and moderation, to promote contact among its users.

**Figure 2 F2:**
[figure not shown]
Home page and sections of Prevencanadol program website.

The information posted by the adolescents in the discussion forum encourages the creation of a list of advantages, which is suitably prepared by experts and is sent weekly by SMS to the students. These SMS are intended (a) to serve as convincing arguments in order to stop risk behaviors and (b) to facilitate self-efficacy when implementing the cancer prevention guidelines. An example of a SMS focused on a healthy diet is the following: ‘*Don*’*t be fooled*! *The best way to be pretty on the outside is by being pretty on the inside*. *Fruits and vegetables are your best makeup*’.

### Intervention procedure

Many national and local organizations have supported Prevencanadol and have even participated in its diffusion by embedding links to our program website (http://www.alertagrumete.com) on their own institutional websites. In addition, Spanish and Mexican educational administration departments sent a massive email to all the teachers of Secondary Education, in which they explained the project and encouraged participation.

Individuals, that join voluntarily, must formalize their register in the website by providing an alias, an avatar and a private password. To complete the registry, they must fill in a compulsory online questionnaire (pre-test). After that, the computer system randomly assigns that person to one of the groups of study. Participants of the CG will have limited access to the described sections. However, those of the EG will be allowed to participate in all the proposed activities, from that very moment. At the end of each academic year, all the participants will be required to complete the same questionnaire again (post-test).

Prevencanadol is conceived as a competition: participants can obtain points in all the activities. They can receive points by different ways, such as answering the questionnaires, visiting the web for more than three minutes, watching videos, posting comments or enrolling other participants, among others. But, above all they will obtain points by solving didactic challenges. Those students and schools with the highest scores will receive a present; and they will be able to choose between different options, such as computers, mobile phones, sports equipment, books, didactic games, etc.

### Assessment of the impact of the intervention

As previously mentioned, the program also includes a pre- and post- intervention assessment. We will use them to try to determine the existing differences related to the following of the ECAC advice between (a) the very first moment in which the person is registered in the website (i.e., the beginning of the academic year) and (b) the moment in which the intervention period finishes (i.e., the end of the academic year). A complex, anonymous and self-managed questionnaire is used, and it requires approximately 20–30 minutes to be completed. It is based on another one, which has been previously validated by López et al. [29]. Notwithstanding that, it has been adapted to both young population and to online management, since it previously included graphic solutions and contact forms used to answer questions.

The obtained information allows us to design the ‛*main result variable*’, which is a synthetic indicator of the percentage of cancer risk in each individual based on his/her risk behaviors (i.e., the so called ‛global cancer behavioral risk’). This indicator is calculated by simply adding up all the risk points obtained by each person when he/she did follow the ECAC advice (Table 2); that means that a scoring of 100 shows the maximal behavioral cancer risk. These risk points are obtained from the percentage of responsibility for cancer, and according to scientific evidence, every behavior of the participant is responsible for this percentage [5-7,30,31]. To know if the individuals are following or not the advice, we will (a) apply the stages of change pointed out by Prochaska and DiClemente to each behavior and we will (b) use a questionnaire of frequency of food intake (regarding both risk foods and cancer protective foods). This questionnaire also includes information related to many variables, which according to scientific literature could modify the effect, since they influence the following (or lack of following) of the ECAC advice. These variables are: (a) *socio*-*demographic variables* (e.g., age, gender, country of residence – Spain or Mexico –, cohabitation, number of siblings, academic level, academic level of parents, weekly expenses, among others), (b) *family history of cancer* and (c) *determining factors of the A*.*S*.*E*. *Model* (i.e., social influence and self-efficacy for each behavior). Other variables which are related to the educational intervention are also controlled (e.g., SMS delivery, score obtained in the competition, number of months that the student is registered in the website, etc.).

**Table 2 T2:** **How to calculate the indicator**: “**total cancer behavioral risk**” (**principal result variable**)

**Cancer behavioral risk**	**Points**
Smoking	35
Not eating five servings of fruit and vegetables per day	20
Eating three or more daily fatty foods	10
Quotient “frequency of protection food/risk food” ≤0.9	8
Obesity/Overweight	15/10
Excessive drinking	5
Sedentary	5
Ultraviolet radiation exposure without protection	2
Workplace exposure to carcinogens*	5
Maximum punctuation in adolescents	100^†^

*Only in adults. ^†^ 105 points in adults.

The statistical analysis will be performed through multivariate regression procedures (using the ‘Enter’ method) to control the effect of potential confounders and modifiers of the effect. Regressions will follow several steps in order to establish the percentage of variability of the result variable which is explained by the remaining variables.

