**Methods:**

This protocol describes the design and implementation of a complex online program that includes a randomized controlled trial put into practice in two countries: Spain and Mexico. Adolescents and adults of their environment (relatives and teachers) who voluntarily participate will be randomly assigned to the experimental group or to the control group once they have completed the online pre-test. The experimental group members will have free access to a tailor-made and interactive website (http://www.alertagrumete.com). During the academic year, this website will be periodically updated with different school and leisure activities related to the avoidance of risk behaviors. To encourage participation, the program includes a competition that gives rewards to the winners. SMS are also sent to students to stimulate the adoption of healthy behaviors and as a reminder of participation. Finished the intervention, an online post-test is performed in both groups and the impact on the risk behaviors is therefore assessed.

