### Study population and composition of the groups

The study population is composed of Spanish and Mexican students of Secondary Education, aged between 12 and 16, who have voluntarily accepted to participate in an educational program which is managed online and supplemented with the delivery of SMS. Due to the program characteristics, it is required to have access to the Internet at home or at school. However, mobile phones are optional. Adults of the environment of the student (family or teachers) can also participate in the program: (a) they can be previously invited by an adolescent or (b) they can also join spontaneously.

Students and adults should register onto the Prevencanadol website. Then, a computerized and randomized process will distribute them in an experimental group (EG) and in a control group (CG). According to the program characteristics, the randomization is subject to these two requirements: (a) 60% of the users should be assigned to the CG since a higher withdrawal rate is expected in this group; and (b) members of the same classroom or family should share a study group so as to avoid the possible contamination of the groups.

In order to detect a significant decrease (p<0.05) of at least 10 percentage points in the global behavioral risk indicator during the post-test, it will be necessary to recruit 622 individuals in each arm of the study (statistical power = 90% and estimated withdrawals = 20%).

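### A two-arm comparison is intended, but the stated regression target is variance explained, not the EG-minus-CG difference; naming that difference, adjusted for the pre-test score, is a free improvement

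*Protocol article*

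**What the plan says.** Three statements in the Protocol article bear on what will be estimated.

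- *Assessment of the impact of the intervention*, on the purpose of the two questionnaires: to determine "the existing differences related to the following of the ECAC advice between (a) the very first moment in which the person is registered" and the end of the academic year. Both ends of this contrast are time points.
- The same section, on the analysis: multivariate regression by the Enter method is used "to control the effect of potential confounders and modifiers of the effect", in several steps, "in order to establish the percentage of variability of the result variable which is explained by the remaining variables".
- *Study population and composition of the groups*, on sample size: 622 individuals per arm are needed to detect a "significant decrease (p<0.05) of at least 10 percentage points in the global behavioral risk indicator during the post-test". The comparator is not given.

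The outcome is a points score, "a synthetic indicator of the percentage of cancer risk in each individual based on his/her risk behaviors", with a maximum of 100 in adolescents and 105 in adults (Table 2). The same section also lists variables to be taken into account: socio-demographics, family history, A.S.E. factors, and intervention-related variables such as "SMS delivery, score obtained in the competition, number of months that the student is registered in the website". Neither study group nor the pre-test score appears in these lists, which are open-ended.

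Other places make the two-arm intention plain. The Abstract (Methods) says that "an online post-test is performed in both groups and the impact on the risk behaviors is therefore assessed". *Type of study* and the Discussion call the design a randomized controlled trial, which the Discussion says can be considered cluster randomized.

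**The concern.** A randomized trial earns its credibility from the contrast between arms, and the two sentences that say what the analysis is for do not state that contrast.

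The percentage of variability explained is a property of a whole set of predictors and of the spread of the sample. It does not say by how many points the intervention changed the score, or in which direction. Here it would also pool the contributions of age, family history, competition score and the rest.

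A registration-to-end-of-year difference, if read within an arm, would combine the intervention with whatever else changes over a school year. The article's own background says that the main risk behaviors begin and settle in adolescence, so some common change is plausible.

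At stake is whether the main result can be read as an effect in points with its uncertainty, and whether the 10-point target can be checked against it.

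**Working it through.** **1. The plan's own figure.** The sample-size statement gives 622 per arm, 90% power, p<0.05 and 20% withdrawals. It gives no SD, control rate or pre-post correlation, so 622 cannot be derived from stated inputs, and it does not reveal which contrast was meant. With assumed inputs and equal arms:

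- 50% versus 40%, two-sided: 519 per arm, and 519 × 1.2 ≈ 623.
- 40% versus 30% with continuity correction: 496 per arm, and 496 / 0.8 = 620.
- A 10-point difference in mean score: 622 × 0.8 = 497.6 completers implies an SD of about 48.7.

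The point made here does not depend on which of these was used.

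**2. Why variance explained does not convey the effect.** For a difference δ between arms with allocation fractions p and 1−p and within-arm SD σ, arm alone explains

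R² = p(1−p)δ² / [σ² + p(1−p)δ²].

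With the article's 60:40 allocation and δ = 10, p(1−p)δ² = 0.24 × 100 = 24. For assumed SDs:

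- σ = 10: 24/124 = 19.4%
- σ = 20: 24/424 = 5.7%
- σ = 30: 24/924 = 2.6%

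The same 10-point effect gives figures that differ more than sevenfold, and δ = −10 and δ = +10 give the same value.

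**3. What a within-arm time contrast would do, if that were the analysis.** Assumed: SD 20, correlation 0.6, no intervention effect, and 498 completers per arm (622 × 0.8). The SD of change is 20 × √(2 × 0.4) = 17.9, with standard error 17.9/√498 = 0.80. Simulated proportion of trials significant at 0.05:

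| Common change (points) | Within-arm pre-post test | Between-arm test |
|---|---|---|
| 0 | 5% | 5% |
| 1 | 23% | 5% |
| 2 | 70% | 5% |
| 3 | 96% | 5% |

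For scale, smoking carries 35 points in Table 2. A common shift of 1 to 3 points therefore corresponds to a change in smoking prevalence of 1/35 to 3/35, or 2.9 to 8.6 percentage points. The article gives no yearly trend. A common rise in risk would hide a benefit instead of mimicking one.

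**4. What the pre-test score adds.** With pre-post correlation ρ and equal variances, the variance of the arm effect relative to a post-test-only comparison is 2(1−ρ) for change scores and 1−ρ² after baseline adjustment. The ratio of adjusted to change-score variance is (1−ρ²)/[2(1−ρ)] = (1+ρ)/2.

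| ρ (assumed) | Change score | Adjusted | Reduction vs post-test only | Reduction vs change score |
|---|---|---|---|---|
| 0.3 | 1.40 | 0.91 | 9% | 35% |
| 0.5 | 1.00 | 0.75 | 25% | 25% |
| 0.6 | 0.80 | 0.64 | 36% | 20% |
| 0.7 | 0.60 | 0.51 | 49% | 15% |
| 0.8 | 0.40 | 0.36 | 64% | 10% |

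These factors ignore clustering. *Intervention procedure* makes the pre-test compulsory before the system assigns a person to a group, so the covariate exists for every participant.

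**The case against.** The strongest reply is that a difference over time, compared between groups, fits every sentence in the article. The trial is called randomized and controlled, both groups take the post-test, the sample size is stated per arm, and controlling modifiers of the effect presupposes an intervention effect. An Enter regression also produces coefficients, and nothing says that only variance explained will be reported.

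That reply stands against two stronger readings that a reader might infer.

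- *That the plan fixes impact as an uncontrolled within-group change.* The impact section says which two moments are compared, not that the comparison stays within one arm. Common change cancels in any comparison of the arms, so the table of false positives shows what the wording leaves open, not what the plan prescribes.
- *That the plan leaves out the pre-test score.* The variable lists are open-ended and concern other questionnaire items. An article condenses a fuller plan, so silence on a covariate, on the arm term or on a confidence interval is not in itself a defect.

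Nor can both harms be charged at once: if the regression yields the variance explained by arm, it is already comparing arms.

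What the reply does not remove is the stated goal of the regression steps. That is something the article says, not something it omits, and a separate analysis plan would have to replace it. The missing comparator for the 10-point decrease also remains.

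**Conclusion.** The point holds in limited form. A two-arm comparison is intended, but the article aims its regression at variance explained, describes impact only as registration versus end of year, and does not say what the 10-point decrease is measured against. None of these is the randomized effect in points.

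This is a free improvement, not evidence that the trial's conclusion would be biased. The gain is an interpretable primary result and, with baseline adjustment, a variance of the arm effect lower by about 9% to 64% than post-test only and by about 35% to 10% than change scores, for correlations of 0.3 to 0.8. Those correlations, and the SDs and common changes used in the illustrations, are assumptions, since the article gives none of them. The size of the gain is therefore uncertain, although its direction is not in doubt for positive correlations.

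**What to change.** - In *Assessment of the impact of the intervention*, name the primary estimate: the EG-minus-CG difference in mean end-of-year global risk score, with a 95% CI, from a regression of post-test score on study group and pre-test score that allows for allocation by classroom and family.
- Keep the percentage of variability explained as a descriptive summary only.
- In *Study population and composition of the groups*, state that the 10-point decrease is relative to the control group.

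The cost is a few sentences. The pre-test score is already collected from every participant, and recruitment, questionnaires and follow-up do not change.

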### Ethical considerations

This intervention was approved by the Spanish Ministry of Health (*FISS08PI080544*) and by the Clinical Research Ethical Committee of the Principality of Asturias (Spain) (*no*. *19*/*09*). In Mexico, methodological and ethical considerations were approved by the Subsecretary of Public Education.

## Discussion

In this section we aim to discuss the main features of the methodological design of Prevencanadol:

Firstly, the project complies with the basic requirements for a parallel randomized controlled trial: (a) the study factor is artificially manipulated (online educational intervention and delivery of SMS) and (b) the study population is randomly distributed to an EG and to a CG. Notwithstanding that, this randomization is determined by the first registered student of a classroom, and consequently real classroom randomization is achieved. From this standpoint, this trial can be considered a cluster randomized controlled trial, which is a very useful design to avoid the possible contamination of the groups. However, an important limitation of the experimentation with educational interventions is that it is not possible to guarantee that participants have received the content of the intervention, as it could be done if it were a pill, for instance. But Prevencanadol has managed to reduce this limitation since it has incorporated in the statistical analysis the scoring obtained during the competition, which is an indirect indicator of the reception degree of the intervention.

Secondly, as already pointed out, the program addresses a target population between 12 and 16 years old in order to reach the highest cancer preventive efficacy, since adolescence is a vital stage in which many behaviors (that will shape the adult stage) are acquired and consolidated. Although it can be a difficult age range, prevention of risk behaviors in this population group is also possible, especially if advice is linked to the school context [32-34]. However, it is not a task that is exclusively linked to school: we should bear in mind that society and family can be important sources of behaviors [35], and therefore we also encourage the registering of adults (teachers and family) in the website http://www.alertagrumete.com. In this way, it is even possible that healthy adolescents also become instigators of some preventive behaviors among adults; that consequently achieves ascending education. Finally, regarding the diversity of participants, we should also mention that we could only have included in the program adolescents with established risk behaviors, as other authors do in their works [36], but in our opinion when working with such a young population, it is as necessary to treat existing risk behaviors as well as to prevent their presence.

Thirdly, as the intervention is both school- and web-based, it is required that adolescent participants are currently attending school and have Internet access available. In relation to the first requirement, we can affirm that about 5.4% and 13.2% of the Spanish and Mexican adolescents respectively do not regularly attend school [37], usually because they belong to disadvantaged environments. Regarding the second condition, we can conclude that in Spain almost all schools have Internet access [38], but in Mexico only less than half comply with this requirement [39]. Due to these two reasons, the intervention could be confined only to those families and schools with a higher socioeconomic level.

Fourthly, the chosen educational tools (Internet and SMS) are novel in the field of Health Education and can be easily adapted to young population. In addition, students and teachers of Secondary Education helped with the web design in order to avoid the refusal of the participating students, since it is well-known that planning this kind of interventions without bearing in mind the likes of the target population could cause them to fail even before they have been implemented [40]. However, the vertiginous evolution of this kind of technologies may have clouded the originality of this initiative, since nowadays global social networks (such as *Facebook*, *Twitter*, *Ozone*, etc.) have completely changed the way in which the web is understood. It might have even caused a certain lack of interest in the users towards other kinds of websites or minority social networks, as this one we have tried to create through http://www.alertagrumete.com.

Lastly, we would like to mention that Catalano et al. [41] published in 2012 an interesting manuscript that seems to support the approach of Prevencanadol since: (a) they acknowledge it is necessary to involve state workers (in this case, teachers) in the program; (b) these authors also suggest the identifying of both the problems and the groups in which an educational intervention is urgently needed (this is one of the aims of Prevencanadol, which we have highlighted above); and specially (c) they highlight that it is necessary to prove the efficacy of these initiatives in lower-middle income countries, as well as to find factors in these countries that can be different to those found in richer countries (and that is exactly what this program has done in Mexico).

To sum up, Prevencanadol could be considered groundbreaking, since it (a) aims to link family and school environments, (b) combines the use of the Internet and the delivery of SMS, (c) considers psychosocial models which are supported internationally, (d) intervenes in six behaviors simultaneously, and (e) compares the efficacy of the intervention in a country with a high income level (Spain) with that obtained in another one with a middle income level (Mexico).

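### The first registrant fixes a classroom's arm, so every later member enrols and takes the pre-test after allocation, which leaves room for recruitment bias and early second-hand exposure

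*Protocol article*

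**What the plan says.** The protocol article describes allocation in two ways.

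- **Individual assignment after the pre-test.** In the Abstract (Methods), participants "will be randomly assigned to the experimental group or to the control group once they have completed the online pre-test". The Intervention procedure makes the pre-test a compulsory part of registration and continues: "After that, the computer system randomly assigns that person to one of the groups of study".
- **Allocation by cluster.** The section on study population and composition of the groups requires that "members of the same classroom or family should share a study group so as to avoid the possible contamination of the groups". The Discussion adds that "this randomization is determined by the first registered student of a classroom" and treats the result as genuine randomization of classrooms.

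On access, the Intervention procedure says "Participants of the CG will have limited access to the described sections", whereas "those of the EG will be allowed to participate in all the proposed activities, from that very moment". Joining is voluntary. Ways to earn competition points include "watching videos, posting comments or enrolling other participants", and adults may be invited by an adolescent or may join on their own initiative.

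**The concern.** In a cluster trial, randomization balances the clusters. It balances the individuals in them only if they are identified before the arm is drawn, or if their enrolment cannot depend on it. Here the draw occurs when one student registers, and the rest of the classroom and the linked families enrol afterwards. Two routes to bias follow.

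1. **Recruitment.** Who joins, and how many, may depend on the arm, because joining is voluntary and the two groups' access differs in ways that enrolled classmates can see. The participants could then differ between arms in motivation or starting risk.
2. **Baseline.** A later member of an experimental cluster may have been influenced by classmates, relatives or a teacher before answering the pre-test. That pre-test is then not a clean baseline.

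The impact assessment compares pre-test with post-test, so both routes reach the main result variable. The planned multivariate regression can adjust for measured covariates. It cannot remove unmeasured selection after allocation, nor restore a pre-test that exposure has already changed.

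**Working it through.** **Step 1. Order of events for each kind of participant, as the text stands.**

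| Event | First registrant of a classroom | Later classmate or relative |
|---|---|---|
| Cluster's arm drawn | after own pre-test | already drawn |
| Own registration and pre-test | before the draw | after the draw |
| Others in the cluster already using the full site (experimental group) | no | possibly |
| Own access set by arm | after own pre-test | after own pre-test |

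The first column matches the Abstract and the Intervention procedure. The second follows from the sharing rule in the study-population section and from the Discussion. The two accounts agree only for the first registrant.

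**Step 2. Share enrolled after the arm is fixed.** With N participants in K clusters and one person per cluster enrolled before the draw, the share enrolled after it is (N − K)/N = 1 − 1/m, where m = N/K is the mean number of registrants per cluster. The article gives no cluster size, so every m below is an assumption.

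| m (assumed) | 1 − 1/m |
|---|---|
| 2 | 50% |
| 3 | 67% |
| 5 | 80% |
| 10 | 90% |
| 25 | 96% |

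If a quarter of all participants were sole registrants (also an assumption), the share would be 0.75 × (1 − 1/m), with m now the size of the remaining clusters: 60% at m = 5, 67.5% at m = 10, about 71% at m = 20.

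This is the share open to the problem. It does not count people who knew their arm or were exposed, and it is not an estimate of bias.

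**Step 3. Is registration simultaneous?** The section on assessment of the impact equates registration with the start of the academic year. The same section lists months since registration as a variable to be controlled, which implies that dates differ. Some time gap is therefore expected; its length is not given.

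**Step 4. Direction.** If a fraction f of experimental participants had their pre-test risk score lowered by d through early exposure, the group's mean pre-to-post reduction would be understated by f × d, so this route pulls toward no effect. Neither f nor d is given. The recruitment route could act either way, so the net direction cannot be stated.

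The planned 622 per arm does not enter these steps and does not change.

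**The case against.** The best defence is that the article declares its cluster features. The sharing rule stands in the methods and the Discussion calls the design a cluster randomized trial, so the individual-assignment wording is condensed rather than deceptive. Keeping classmates together also limits contamination between arms. Both points are fair, but neither deals with enrolment after the draw, which the article does not acknowledge.

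A reader might infer four stronger things that the article does not support.

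- **That later registrants are told their arm before the pre-test.** No announcement is described. The compulsory pre-test precedes any arm-dependent access, so a person cannot use the experimental site before their own baseline. Earlier knowledge would have to come by word of mouth. That is plausible where access differs visibly within a class, but it is not documented.
- **That almost everyone enrols after allocation.** This needs about 10 or more registrants per cluster and few sole registrants. Families are small clusters and adults may join alone.
- **That enrolment points drive recruitment toward one arm.** The points are described for participants in general, and nothing limits them to the experimental group. A common incentive does not by itself produce a difference between arms.
- **That the bias is known to run toward no effect.** This fits the baseline route only.

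Registration near the start of the year would shorten the time for exposure before the pre-test. This limits the harm but does not remove it, given the staggering implied by the months-registered variable.

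**Conclusion.** The concern holds as a design weakness that follows from the procedure as written, not from detail left to a fuller document. All cluster members after the first register and take the pre-test after the arm is fixed and, in experimental clusters, possibly after the intervention has begun around them. The Abstract and the Intervention procedure are correct only for first registrants and must be reconciled with the study-population section and the Discussion.

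The order of events is certain. The share affected depends on an unstated cluster size: half at two registrants per cluster, a clear majority from three upward if sole registrants are few, and 90% or more from ten upward. Arm-dependent recruitment and second-hand exposure are possible rather than shown, and the size and net direction of any bias are unknown.

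**What to change.** 1. **Classrooms not yet started.** Open a short fixed window, collect the registrations and pre-tests of the classroom and its linked families, then draw the arm and unlock access. Cost: a small change to the registration logic and a short delay before experimental access.
2. **Clusters already allocated.** The Discussion speaks of the work in Mexico as done, so this may be the main case. Use registration dates, which the months-registered variable implies are held, to report numbers enrolled and pre-test scores by arm and registration order. Add a sensitivity analysis limited to those who registered within a prespecified interval of their cluster's first registrant. Cost: a smaller sample in that analysis.
3. **Later joiners.** Keep them, and invited adults, in the trial, flagged as enrolled after allocation. Excluding them all from the primary analysis, or suspending enrolment points, is a debatable trade-off, because the adult environment is part of the main aim and recruitment would suffer.
4. **Text.** Reword the Abstract and the Intervention procedure to describe cluster allocation. Qualify the Discussion's claim of genuine classroom randomization by naming recruitment after allocation as a limitation. Cost: editing only.
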